#### Sample size calculation

Using PASS15 software, and a Cox Proportional-Hazards regression model it was estimated that the number of participants needed to examine the primary aim (recovery time in days) is 30. This will allow the detection a hazard ratio of 1.5 (log hazard ratio coefficient = 0.4055), with 80% power, and a type I error rate of 0.05. This was calculated assuming a covariate SD of 1.5, a multiple regression R^2^ (variable of interest regressed on covariates) of 0.2, and an expected event (clinical recovery) rate of 0.9 within the follow-up period. [16, 22] Allowing for 20% drop out during follow-up, 38 participants will be recruited. As of 18 August 2023, 14 eligible women have started the study.

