## Data analysis

In this study a range of statistical tests will be used to analyse the data corresponding to the four aims. Aim 1 will use Cox proportional hazards regression to determine if the time to recovery from concussion (measured in days), differs among groups categorised by hormone profile at the point of injury (five profiles: Follicular phase, Midcycle, Luteal phase, oral contraception, IUD). Aim 2 will apply an ANOVA to compare the ratios of miR-27a-5p/miR-30a-3p expression, across these five groups. Model-estimated means and pairwise contrasts between groups will also be computed. For Aim 3, the focus is on whether self-reported symptoms, quantified both as the number of symptoms present (range 0–16) and as a total symptom burden (sum of severity scores; range 0–160), differ among hormone profile categories. These dependent variables will be analysed using ANOVA, with the five hormone profiles specified as the independent variable. Aim 4 will employ a linear mixed model to investigate changes in low energy availability across the recovery period. This model will incorporate the day of recovery and total symptom burden as fixed effects and will account for repeated measures over time by specifying participant as a random effect. The interaction between symptom burden and recovery time will also be evaluated to understand if these variables are collectively associated with low energy availability.

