### Strengths and limitations of the study

This is the first study to consider the impact of fluctuating female sex hormones on salivary sncRNA expression following concussion. Limitations of this study are that it relies on self-report hormone profiles and does not include verification using the ‘gold standard’ approach [66]. Menstrual cycle information is based on recall which can be subject to bias and inaccuracy. Return to work is being used as a proxy for recovery from concussion which does not necessarily reflect full physiological recovery. Information regarding treatment interventions and follow up appointments for each participant will not be collected, it will therefore not be known how the ongoing management may influence the recovery time. One further limitation could the relatively small sample size compared the number of variables under investigation. The power calculation is based on the primary aim of the study.

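### The 80% power at a hazard ratio of 1.5 is calculated for one quantitative covariate with SD 1.5, not for the planned comparison of five hormone profiles, where power at that hazard ratio is about 7-11%

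*Protocol article*

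**What the plan says.** Under Sample size calculation, the protocol article uses a Cox model and arrives at 30 participants for the primary aim, recovery time in days. It states of this number: "This will allow the detection a hazard ratio of 1.5 (log hazard ratio coefficient = 0.4055), with 80% power". The other inputs are "a type I error rate of 0.05", "a multiple regression R^2^ (variable of interest regressed on covariates) of 0.2", and an event rate of 0.9. The spread of the predictor is given as follows: "This was calculated assuming a covariate SD of 1.5". Neither the variable with that SD nor the sidedness of the test is named. A 20% dropout allowance raises 30 to 38.

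Under Data analysis, Aim 1 is a Cox regression of recovery time on hormone profile at injury, with "five profiles: Follicular phase, Midcycle, Luteal phase, oral contraception, IUD". The section on surveys and questions also assigns each woman to one of five categories (with a somewhat different list) and defines no numeric score.

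Under Strengths and limitations, the article concedes that the sample is small relative to the number of variables, and then states: "The power calculation is based on the primary aim of the study".

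**The concern.** The calculation and the primary analysis describe different predictors. An SD of 1.5 and one log hazard ratio of 0.4055 describe a quantitative variable whose effect is 1.5 per unit. Hormone profile is nominal with five levels, so it enters a Cox model as four indicators and is tested on 4 df, or through contrasts between groups. An indicator has an SD of √(p(1−p)), which never exceeds 0.5. The required number of events varies with 1/SD², so moving from 1.5 to 0.5 or less multiplies the requirement at least ninefold.

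This figure is the only statistical justification given for the sample size. A reader who meets a non-significant Aim 1 result would reasonably take it as 80%-powered evidence against a hazard ratio of 1.5 between profiles. The design cannot provide that evidence.

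**Working it through.** **Inputs from the protocol article.** log HR = 0.4055; SD = 1.5; R² = 0.2; event rate 0.9; type I error 0.05; power 80%; N = 30, hence 30 × 0.9 = 27 events; five profiles.

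**Assumptions, not in the article.** A two-sided test (one-sided would give N = 24, not 30); equal profile shares of 20%, that is 6 women each; and the patterns of difference named below.

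**1. Reproducing the stated figure.** For one covariate in a Cox model,

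D = (z₀.₉₇₅ + z₀.₈₀)² / [SD² × (log HR)² × (1 − R²)]

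- D = (1.960 + 0.8416)² / (2.25 × 0.1644 × 0.8) = 7.849 / 0.2959 = 26.5 events.
- N = 26.5 / 0.9 = 29.5, rounded up to 30.
- With dropout: 30 / 0.8 = 37.5, rounded up to 38.

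The stated figures reproduce. Power at 27 events is 80.7%.

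**2. Same formula and inputs, changing only the SD to that of a group indicator.** Power = Φ(√(27 × SD² × (1 − R²)) × 0.4055 − 1.960).

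| Contrast | SD | Power at HR 1.5, 27 events | Women needed for 80% |
|---|---|---|---|
| 50:50 (largest possible SD) | 0.5 | Φ(0.942 − 1.960) = 15% | 266 |
| One 20% profile v the rest | 0.4 | Φ(0.754 − 1.960) = 11% | 415 |

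With R² = 0 the two powers are 18% and 13%.

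**3. The five-group comparison on 4 df.** Noncentrality = 27 × Var(group log HR) × (1 − R²); the 5% critical value of chi-square on 4 df is 9.49.

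| Pattern at HR 1.5 | Var(log HR) | Power, R² 0.2 to 0 |
|---|---|---|
| One profile v four | 0.16 × 0.1644 | 8.0-8.8% |
| Two profiles v three | 0.24 × 0.1644 | 9.7-11.0% |
| Evenly spread, extremes differ by 1.5 | 0.125 × 0.1644 | 7.3-7.9% |

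A single pair (6 v 6, 10.8 events) has about 10%. If all 38 women gave data (34.2 events), the three 4-df patterns have 8-13%.

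In simulation with 6 women per group, the nominal 4-df log-rank (Cox score) test rejected about 11% of the time under the null. With the critical value calibrated to a true 5%, power for these patterns was 6-8%, so the approximation is not pessimistic.

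**4. Where an SD near 1.5 might come from.** Codes 1 to 5 in equal groups have SD √2 = 1.41 (1.58 with divisor n − 1). A hazard ratio of 1.5 per step then means 1.5⁴ = 5.06 between the first and last profile. Even if that were true, the 4-df test with 27 events would have only 55% (R² 0.2) to 66% (R² 0) power.

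**5. Hazard ratio detectable with 80% power at 27 events.** The 4-df test needs noncentrality 11.94, so HR = exp√(11.94 / [27 × v × (1 − R²)]), where v is 0.24 or 0.16 as in step 3.

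- Two v three profiles: 3.9 (R² 0) to 4.6 (R² 0.2).
- One v four profiles: 5.3 (R² 0) to 6.4 (R² 0.2).
- One 60:40 two-group contrast, exp(2.802 / √[27 × 0.24 × (1 − R²)]): 3.0 (R² 0) to 3.4 (R² 0.2).

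The 4-df values are optimistic at this size. In simulations at HR 3.9 and 5.3 for the matching patterns, size-calibrated power was about 56-68%, not 80%.

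**The case against.** The arithmetic is correct for its inputs, so it would be wrong to infer a calculation error; the fault is that the inputs do not match the planned analysis.

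A reader might also infer that the profiles were scored 1 to 5. The article does not say so. It never names the variable with SD 1.5, and equal-sized codes 1 to 5 give 1.41 or 1.58 rather than 1.5. The conclusion does not need that inference: whatever the variable is, the bound of 0.5 shows that it is not a group indicator.

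Group shares and the pattern of differences are not stated, so no single power figure, such as 10%, can be claimed. That stands for the 4-df range. The 15% ceiling for a two-group contrast holds for any shares, given R² = 0.2, and unequal groups would usually lower power further. The list of five profiles also differs between the survey section and the data analysis section, but both lists are nominal with five levels.

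The article does admit a relatively small sample. It does not correct the power statement, and it restates that power was based on the primary aim. Nor does it say how a null result would be interpreted; the risk described above is what a reader could reasonably conclude. Finally, a separate analysis plan could add detail, but it would not make this explicit statement agree with the Aim 1 analysis beside it.

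**Conclusion.** The point holds as a mismatch between the sample size calculation and the primary analysis. The statement of 80% power at a hazard ratio of 1.5 is not a property of the five-profile comparison. At that hazard ratio, power is at most about 15% for any two-group contrast (with the protocol's R² and event rate). It is about 7-11% for the 4-df test, assuming five equal groups, 27 events and R² between 0 and 0.2.

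Two stronger readings are not supported. One is that 30 women have 80% power for hazard ratios of roughly 4 to 5. That rests on R² = 0 and a large-sample approximation that is optimistic with 6 women per group; at the protocol's R² the same approximation gives 4.6 to 6.4. The other is that the study must be enlarged. The documents support only the conclusion that the stated power is wrong for this analysis, and an estimation study of this size can be reported honestly.

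**What to change.** Keep the sample size and withdraw the claim of 80% power for a hazard ratio of 1.5 between profiles. Name the variable to which the SD of 1.5 belongs, or drop that input.

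Recalculate for the analysis actually planned, either the 4-df test or one pre-specified two-group contrast (for example naturally cycling v contraceptive users). State the group shares and R², and report the resulting detectable hazard ratio. As a guide, the large-sample approximation gives about 3.9-6.4 on 4 df and about 3.0-3.4 for a 60:40 contrast. Confirm the 4-df figure by simulation with the type I error controlled, because the approximation flatters a design with 6 women per group.

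Present Aim 1 as estimation with confidence intervals, and say that a non-significant result is not evidence of no difference. Amend the sentence on power under Strengths and limitations to match.

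The cost is a short recalculation and rewording, with no extra participants. The downside is a less favourable stated figure.

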### Procedures and measures

Data collected from participants includes two saliva samples and two different surveys administered online weekly until the participant reports a full return to work/study.

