**Methods:**

This prospective cohort study recruits participants from New Zealand EDs who are biologically female, of reproductive age (16–50 years) and with a confirmed diagnosis of concussion from an ED healthcare professional. Participants are excluded by ED healthcare professionals from study recruitment as part of initial routine assessment if they have a pre-diagnosed psychiatric condition, neurological condition (i.e., epilepsy, cerebral palsy) or more than three previously diagnosed concussions. Participants provide a saliva sample for measurement of sncRNA’s, and online survey responses relating to hormone profile and symptom recovery at 7-day intervals after injury until they report a full return to work/study. The study is being performed in accordance with ethical standards of the Declaration of Helsinki with ethics approval obtained from the Health and Disability Ethics Committee (HDEC #2021 EXP 11655), Auckland University of Technology Ethics Committee (AUTEC #22/110) and locality consent through Wellington hospital research office.

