#### Participants and recruitment

Females presenting to ED within three days of injury with suspected concussion are recruited by ED healthcare professionals. Participants are invited to participate if they are biologically female (self-report), of reproductive age (16–50 years) and have a confirmed diagnosis of concussion from the consulting healthcare professional. The diagnostic criteria for concussion are those outlined in the most recent international consensus statement from the concussion in sport group. [51] Participants will be excluded if they have Polycystic Ovarian Syndrome (PCOS), a pre-diagnosed psychiatric disorder or neurological condition (e.g. epilepsy, cerebral palsy) or if they have had more than three previously diagnosed concussions; these are known modifiers for prolonged recovery. [52, 53] These specific exclusion criteria will be ascertained by the consulting ED healthcare professional as part of the initial routine assessment for concussion. Full inclusion/exclusion criteria are shown in Table 1. The standard concussion assessment is detailed in Fig. 1. Study recruitment commenced February 2022, however there was interruption due to COVID related sickness and changes in the ED through November 2022. The study recommenced in January 2023 and is in progress.

**Table 1 Tab1:** Inclusion and exclusion criteria

Inclusion criteria	Exclusion criteria
Females of reproductive age: 16–50 years (with a menstrual cycle for a minimum of 2 years if naturally cycling)	Had three or more previously diagnosed concussions
Natural regular menstrual cycle 28–35 days long, or Currently taking Oral Contraceptive Pill (OCP), or Currently have Intra Uterine Device (IUD), or	Current concussion was more than 3 days ago
	Post-menopause
	Started taking medication that would alter reproductive hormone concentrations (Corticosteroids, e.g., Prednisone. Antidepressant or Antipsychotic medication) within the last 3 months
	Current clinical diagnosis of an eating disorder
	Pre-diagnosed psychiatric disorder
	Pre-diagnosed neurological condition
	Polycystic Ovarian Syndrome (PCOS)
	Oligomenorrheic (irregular periods), or
	Amenorrheic (loss of periods for 3 months or longer)
Confirmed diagnosis of concussion by a medical doctor (within 3 days of injury)	GCS^a^ score less than 15 at 4 h after initial assessment. These patients may be referred for a CT scan and will not be eligible for the study

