#### Saliva samples

Participants will be asked to provide a 2 ml saliva sample. The sample, will be used to measure sncRNAs, and will be collected in SpeciMax stabilised saliva collection kits (Thermo Scientific SpeciMAX stabilised Saliva Collection Kit A50697, Life technologies Corp, Austin, Texas USA) which are pre-filled with 1 ml of virus inactivating and nucleic stabilization solution. Tubes are pre-labelled with a unique barcode linked with each participant’s unique identifier number. All samples are collected using a passive drool method. [55] Before providing each sample, participants take a small sip of water, swish the water around in their mouth and then swallow the water. This stimulates saliva release and clears any food debris that may be in the mouth. The participant’s approximate last mealtime is noted as this may influence saliva sample quality. The saliva sample is immediately stored in the freezer at − 80 °C until all samples are collected. Samples are then couriered on dry ice to laboratories in Auckland for processing and analyses.

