**Table 2 Tab2:** Research measures and collection points

Measure	How	Who	When		
			Initial assessment	During recovery (7-day time intervals)	Full return to work/study
Saliva Samples	Passive drool into cryovial	Consulting clinician, research assistant or Lead Researcher	X		
Number of prior concussions^b^	Online^a^	Participant to complete		X	
Sport or non-sport related concussion^b^	Online^a^	Participant to complete		X	
LEAF-Q	Online^a^	Participant to complete		X	
BIST	Online^a^	Participant to complete	X	X	
Number of days from injury to recovery (full return to work/study)	Online^a^	Participant to complete			X

^a^Weblink emailed to participant

^b^Question only asked once, at first (7-day) timepoint

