## Discussion

There is a lack of female specific sports science and biomedical research. [20, 60–65] Previous studies investigating candidate biomarkers for concussion have either been conducted in exclusively male cohorts or have not considered the influence that fluctuations in circulating sex hormones may have on the expression of salivary biomarkers. This protocol is important as it will help to determine whether females with a suspected concussion have similar salivary sncRNA expression to those reported in the literature for male athletes [35] and highlight any potential for false negative or positive results when considering salivary biomarkers as a diagnostic tool for females with suspected concussion. If this study confirms presence of sncRNAs in females with concussion, it will provide evidence of the potential of saliva sampling as an objective tool to aid in diagnosis of and confirmation of recovery from concussion. Findings will highlight whether expression and ratio of two sncRNAs may be associated with sex hormones in females and therefore whether this would be a feasible and reliable tool for routine clinical use in this cohort. Findings will also highlight how different hormone profiles may be associated with concussion symptom severity and duration in females.

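### The article gives two saliva samples in one place and one elsewhere; as scheduled, with no recovery sample and no non-concussed women, its statements on diagnosis, confirming recovery and false positives are not supported

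*Protocol article*

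**What the plan says.** On the number of samples, the protocol article is inconsistent:

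- Procedures and measures: "Data collected from participants includes two saliva samples and two different surveys administered online weekly". No timing is given for the two samples.
- Abstract, Methods: "Participants provide a saliva sample for measurement of" sncRNAs, in the singular.
- Saliva samples: "Participants will be asked to provide a 2 ml saliva sample", again in the singular.
- Table 2: the saliva row ("Passive drool into cryovial", collected by "Consulting clinician, research assistant or Lead Researcher") has one mark, under the initial assessment. The columns for the recovery period and for full return to work or study are empty.

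On who is sampled, Participants and recruitment invites women who "have a confirmed diagnosis of concussion from the consulting healthcare professional", and Table 1 repeats the requirement. No non-concussed or pre-injury comparator is described.

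On analysis, the Data analysis section gives saliva one method: an ANOVA of the miR-27a-5p/miR-30a-3p ratio across five hormone profiles, with group means and pairwise contrasts (Aim 2).

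On conclusions, the Discussion says that finding sncRNAs in concussed women would be evidence for saliva as a potential "objective tool to aid in diagnosis of and confirmation of recovery from concussion". The abstract makes the same statement. The Discussion adds that the study will "highlight any potential for false negative or positive results when considering salivary biomarkers as a diagnostic tool for females with suspected concussion".

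**The concern.** Two things are at stake. The first is what staff collect. A reader of Procedures and measures would expect two samples per woman, and a reader of Table 2 would take one. A recovery sample that was never taken cannot be obtained later, and 14 women had already started by 18 August 2023.

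The second is what may be concluded. A claim about confirming recovery needs a measurement at or after recovery. A claim about diagnosis or false positives needs people without concussion. If neither is present, finding these RNAs in injured women does not bear on either claim, and a reader of the eventual report could be misled about what was tested.

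**Working it through.** **1. Number of women.** The sample size section gives 30, raised to 38. With log hazard ratio 0.4055, covariate SD 1.5, R² 0.2, event rate 0.9, two-sided alpha 0.05 and 80% power:

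- events = (1.960 + 0.842)² / (1.5² × 0.4055² × 0.8) = 26.52
- women = 26.52 / 0.9 = 29.47, rounded up to 30
- with 20% dropout, 30 / 0.8 = 37.5, rounded up to 38

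The figure reproduces. It serves here only as a denominator.

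**2. Number of samples.** One place says two, two places use the singular, and the schedule table marks one occasion. Two samples could mean an acute and a recovery sample, which contradicts Table 2. It could also mean two tubes at the first visit, which fits Table 2 but not the singular in the Saliva samples section. The text does not decide between them. Under Table 2 the number of recovery samples is 0 of 38 on either reading, so within-woman change cannot be computed.

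**3. Place for a second sample in the analysis.** The Aim 2 ANOVA has one factor, hormone profile, and no time or participant term. In the same section Aim 4 is given a linear mixed model with participant as a random effect. The authors name repeated measures where they intend them, and name none for saliva.

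**4. Diagnostic quantities.**

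- Specificity = true negatives / non-concussed women. The denominator is 0, so specificity and the false-positive rate are undefined.
- False-negative rate = concussed women classed as negative / all concussed women. The denominator exists (up to 38), but the numerator needs a cut-off for the ratio, and the article states none.
- Detection in cases says nothing about how often the same RNAs are detected in women without concussion. The article's own precedent (section on sncRNA expression analysis) rested on a lower ratio in 75 concussed than in 97 non-concussed people, and its 73.3% specificity came from having that second group.

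**5. How rough a false-negative estimate would be.** As an illustration only, assume that an external cut-off is supplied and that sensitivity is close to the cited 82.4%:

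| Women | Classed positive | Sensitivity, exact 95% CI | False-negative rate, 95% CI |
|---|---|---|---|
| 38 | 31 | 82% (66% to 92%) | 18% (8% to 34%) |
| 30 | 25 | 83% (65% to 94%) | 17% (6% to 35%) |

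These intervals are for the whole cohort. Within any one of five profiles they would be wider.

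**6. What the design does support.** It can estimate the acute ratio by hormone profile and the contrasts between profiles. If the ratio differs, a single threshold might behave differently by profile, and that can be said without a control group.

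**The case against.** The strongest reply is that no aim is touched. The Aim section contains no diagnostic-accuracy or recovery-biomarker objective. Aim 2 asks only about the ratio by profile at injury, and one acute sample answers that. Aims 1, 3 and 4 do not use saliva. The disputed sentences stand in the abstract and the Discussion, and they speak of potential, not of estimated rates. All of this stands, and it sets the severity.

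It can also be said that Fig. 1 is not shown and might place a second sample, that the Saliva samples section speaks of each sample, which is compatible with more than one, and that a full protocol or analysis plan might hold a paired analysis or a cut-off. This stands in part. It rules out saying that recovery data are being collected and wasted, which a reader might infer: the article does not establish that a second sample exists, and stored samples would not be lost. It does not remove the conflict, because a second sample in Fig. 1 would itself contradict Table 2.

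Finally, false negatives are not wholly out of reach, because confirmed cases and an external cut-off would suffice. This stands too, within the precision shown above. It does not extend to false positives or to recovery, where hedged wording cannot supply the missing controls or the missing sample.

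**Conclusion.** The point holds, with limited reach. The article contradicts itself on the number of saliva samples. On the schedule in Table 2 there are 0 recovery samples and 0 non-concussed women. The statements on confirming recovery, on diagnostic value and on false positives are therefore unsupported by the design. False negatives could be examined only roughly and only with an external cut-off.

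A reader might infer that the study's main conclusions fail, or that no statement about misclassification is possible. The documents do not support either. The four aims stand, the statements at issue are hedged discussion text, and a difference between profiles would legitimately raise the question of a common threshold.

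This should be fixed but is not critical. It rests on Table 2 being the operative schedule and on no comparator group existing outside the article. If a recovery sample is in fact taken, within-woman change becomes estimable, but the limits on diagnosis and false positives remain.

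**What to change.** Reconcile the abstract, Procedures and measures, Saliva samples and Table 2 so that they give the same number of samples and the same timing.

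- If a second sample is collected, mark its timepoint in Table 2 and add a paired analysis of the within-woman change in log ratio. Menstrual phase may also have moved between the two samples, so the weekly LEAF-Q answers should be used to describe phase at the second one.
- If only one is collected, change two to one in Procedures and measures and remove confirmation of recovery from the abstract and the Discussion.

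In either case, limit the saliva conclusion to whether the acute ratio differs between hormone profiles among concussed women, and so whether a single threshold might behave differently by profile. Make no claim on diagnostic discrimination or false positives. If false negatives are to be mentioned, state the external cut-off in advance and report the interval.

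The cost is wording only if there is one sample, and one table entry plus one analysis if two are already being taken. Neither changes the sample size or the four aims.
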